# An app with brief behavioural support to promote physical activity after a cancer diagnosis (APPROACH): study protocol for a pilot randomised controlled trial

**DOI:** 10.1186/s40814-022-01028-w

**Published:** 2022-03-29

**Keywords:** Cancer, Pilot, RCT, Brisk walking, Physical activity, App, Habit

## Abstract

**Background:**

There are multiple health benefits from participating in physical activity after a cancer diagnosis, but many people living with and beyond cancer (LWBC) are not meeting physical activity guidelines. App-based interventions offer a promising platform for intervention delivery. This trial aims to pilot a theory-driven, app-based intervention that promotes brisk walking among people living with and beyond cancer. The primary aim is to investigate the feasibility and acceptability of study procedures before conducting a larger randomised controlled trial (RCT).

**Methods:**

This is an individually randomised, two-armed pilot RCT. Patients with localised or metastatic breast, prostate, or colorectal cancer, who are aged 16 years or over, will be recruited from a single hospital site in South Yorkshire in the UK. The intervention includes an app designed to encourage brisk walking (Active 10) supplemented with habit-based behavioural support in the form of two brief telephone/video calls, an information leaflet, and walking planners. The primary outcomes will be feasibility and acceptability of the study procedures. Demographic and medical characteristics will be collected at baseline, through self-report and hospital records. Secondary outcomes for the pilot (assessed at 0 and 3 months) will be accelerometer measured and self-reported physical activity, body mass index (BMI) and waist circumference, and patient-reported outcomes of quality of life, fatigue, sleep, anxiety, depression, self-efficacy, and habit strength for walking. Qualitative interviews will explore experiences of participating or reasons for declining to participate. Parameters for the intended primary outcome measure (accelerometer measured average daily minutes of brisk walking (≥ 100 steps/min)) will inform a sample size calculation for the future RCT and a preliminary economic evaluation will be conducted.

**Discussion:**

This pilot study will inform the design of a larger RCT to investigate the efficacy and cost-effectiveness of this intervention in people LWBC.

**Trial registration:**

ISRCTN registry, ISRCTN18063498. Registered 16 April 2021.

**Supplementary Information:**

The online version contains supplementary material available at 10.1186/s40814-022-01028-w.

## Background

There are approximately 2.9 million people living with and beyond cancer (LWBC) in the UK, expected to rise to 4 million by 2030 [1]. People LWBC are at risk of adverse consequences of cancer and treatments, including fatigue, pain, osteoporosis, hypertension, cardiovascular disease, secondary cancers, anxiety, fear of cancer recurrence, and depression [2–6]. As a result, people LWBC often experience poorer quality of life and reduced survival when compared to the general population [2, 3, 7]. Developing interventions that can mitigate some of the negative effects experienced by people LWBC is therefore a public health priority [8].

A large body of evidence shows that physical activity has multiple benefits following a cancer diagnosis. Observational data suggest that people LWBC who are more active have reduced risk of cancer-specific and all-cause mortality (in the region of 25–41%), reduced risk of cancer recurrence, and experience less fatigue, pain, anxiety, depression, sleep disturbance, and better quality of life [9–11]. A recent review, including 679 exercise trials in people LWBC demonstrated that exercise training is safe across the cancer continuum and has beneficial outcomes on both physical and psychological functioning [12]. The evidence for the benefits of physical activity is particularly strong for breast, prostate, and colorectal cancer, three of the most commonly diagnosed cancers worldwide [12, 13]. Given the benefits, the World Cancer Research Fund recommends that people LWBC should aim for ≥ 150 min of at least moderate-intensity physical activity per week [14]. However, it is estimated that less than 30% of people LWBC are meeting these guidelines [15].

The Independent Cancer Taskforce has recommended that everyone diagnosed with cancer in the UK should receive physical activity advice as part of their routine care [16]. However, research from our group found that people LWBC often do not receive physical activity advice from oncology professionals as part of standard care, despite a desire to receive it [17–19]. Healthcare professionals (HCPs) report multiple barriers to delivery, including lack of knowledge of guidelines, feeling that they are not the ‘right person,’ and lack of time and resources [20]. This highlights the need for interventions that are feasible for implementation into care and accessible to a large number of patients. Many trials demonstrating the benefits of physical activity interventions after cancer are supervised by trained professionals, delivered in hospital or community settings, which can lead to high associated costs and limited accessibility [21]. In addition, the COVID-19 pandemic has put pressure on cancer services and changed models of care so it is likely that at least partial remote delivery will be required [22].

Digital interventions have potential for remote delivery of interventions, and smartphone apps are well-positioned as a platform due to their popularity and capabilities. Smartphone ownership continues to increase in all age groups; in 2021, 94% of adults aged over 55 in the UK owned a mobile phone, 83% of which were smartphones [23, 24]. Smartphone apps can track physical activity, deliver ‘in-the-moment’ behaviour change support, and, once developed, can be relatively cost-effective. A meta-analysis of 15 studies conducted by our group found that digital interventions could increase moderate-to-vigorous physical activity (MVPA) participation by approximately 40 min per week in people LWBC [25]. However, only two of these interventions were delivered via apps, and most were small pilot studies and used self-reported physical activity [25]. A subsequent review indicated that smartphone interventions may increase physical activity in people LWBC and that incorporating some element of personal contact could enhance efficacy [26]. This review also highlighted the importance of assessing cost-effectiveness [26]. In order for interventions to have a positive impact on long-term health, they need to promote behaviour change that will be maintained. One route to behaviour maintenance is establishing habits; behaviours which are cued by the contexts in which they are performed, rather than intentionally selected on each occasion they are performed [27]. Habit theory provides a basis on which to provide guidance to help people develop habits [28]. An additional consideration for app-based interventions is a need for sustainability beyond the end of research funding, so utilising/adapting publicly or commercially available apps could have potential.

The design of this study was further informed by qualitative user experience research evaluating existing, publicly available physical activity apps with 31 people diagnosed with breast, prostate, and colorectal cancer. This study identified that people LWBC reported a preference for an app-based physical activity intervention that targeted walking, had elements of tailoring to/recognition of their ability and cancer side-effects, and was endorsed by oncology HCPs and professional bodies [29]. Further qualitative interviews with 19 oncology clinical nurse specialists found that they were generally positive about physical activity apps and felt walking apps would be suitable for their patients before, during, and after treatment [30]. However, they highlighted the need for demonstrated efficacy before they would be willing to recommend them as part of cancer care [30]. Therefore, the ultimate aim of this work is to test the efficacy of an app-based walking intervention, informed by habit theory, and delivered to patients with breast, prostate, and colorectal cancer during their cancer care. The aims of the pilot study are to investigate the feasibility and acceptability of the outcome measures and procedures and obtain initial estimates of the parameters for the intended future primary outcome (device-measured physical activity).

## Trial design

The proposed study is an individually randomised, two-arm pilot RCT comparing an app-based brisk walking intervention delivered alongside standard care, with a control (standard care) arm in people with breast, prostate, or colorectal cancer. The trial has been designed in accordance with the Consolidated Standards of Reporting Trials (CONSORT) statement and its adaptation to pilot trials [31, 32]. See Fig. 1 for a flowchart of the study. The reporting of this protocol follows the Standard Protocol Items: Recommendations for Interventional Trials (SPIRIT) guidelines (see Supplementary Material for a completed SPIRIT checklist) [33] A schedule of enrolment, interventions, and assessments based on the SPIRIT guidelines is shown in Fig. 2.

**Fig. 1 Fig1:**
[figure not shown]
Study flowchart

**Fig. 2 Fig2:**
[figure not shown]
SPIRIT figure—schedule of enrolment, interventions, and assessments

## Eligibility criteria

Participants will be eligible if they have a confirmed diagnosis of breast, prostate, or colorectal cancer at a single hospital site in South Yorkshire, are aged 16 years or older, own a smartphone that uses Android or iOS (Apple) operating systems, are able to provide informed consent, have access to a computer and an email address, and are willing to complete online questionnaires. This hospital serves an area of high deprivation where cancer incidence, mortality, physical inactivity, and obesity are all high compared to the English average [34, 35]. Participants aged 16 and 17 years of age are not excluded from participation as it has been found that this group are keen to be included in cancer research and have often been overlooked in previous research [36, 37].

Exclusion criteria are as follows: having localised disease and it has been more than 6 months since completion of radical treatment (i.e. surgery to remove cancer, radiotherapy, systemic therapy with curative intent), being unable to understand spoken/written English, having an Eastern Cooperative Oncology Group (ECOG) performance status ≥ 3, a diagnosed cognitive impairment (e.g. dementia), a cognitive and/or physical impairment that prevents participation in brisk walking, a clinician-estimated life expectancy of < 6 months, or are receiving end of life care, due to have surgery to remove cancer in the next 5 months, < 6 weeks after surgery to remove cancer, report already achieving 150 min of at least moderate-intensity physical activity weekly, report previous/current use of the intervention app, or report current or recent (< 6 months) participation in a health behaviour change study.

## Sample size

The target sample size for the pilot RCT is 60, with 30 participants allocated to each group. This is based on the rule of thumb that 30 or more participants are required to estimate a parameter in a feasibility study [38, 39]. A total of 90 participants will be recruited to account for potential loss to follow-up (assuming equal drop-out in both groups).

## Recruitment and setting

Research nurses/members of the research team with contractual arrangements at the hospital site will search lists of current breast, prostate, and colorectal cancer patients and examine medical notes to identify potentially eligible participants. At least one clinician with responsibility for the patient’s care will review the list of potentially eligible participants and confirm whether a patient can be approached about the study.

Potentially eligible participants will be sent a letter informing them about the study. Participants who indicate interest will answer a telephone-based eligibility screening questionnaire. If eligible, participants will be sent an email with a link to the online participant information sheet and consent form (administered via REDCap electronic data capture tools hosted at University College London (UCL)) [40, 41]. The consent form (see Supplementary Material) includes asking for optional additional consent to access Hospital Episode Statistics (HES) and the National Cancer Registration and Analysis Service (NCRAS) registries to understand the willingness to consent to long-term follow-up of medical records. In this pilot, we will not access this data, but we ask participants to consent, as we would in a larger trial, in order to understand willingness to consent to this.

## Randomisation

After completion of baseline assessments, participants will be individually randomised using minimisation with a 1:1 allocation ratio. Randomisation will be undertaken centrally using MinimPy (an open source, minimisation programme for allocation of participants to groups in randomised trials) [42]. Randomisation will be stratified by cancer type (breast, prostate, or colorectal) and disease status (advanced/metastatic disease vs. not). After the first participant has been randomly allocated, each subsequent participant will be allocated to the trial arm with the lowest imbalance score, with the addition of a 20% random element to reduce predictability of outcomes. The imbalance score is calculated based on hypothetical allocation of the next participant to each arm [43].

A member of the research team not involved with recruitment or data collection will use MinimPy to generate the allocation sequence as each person is recruited into the study. Intervention participants will be informed about their allocation arm by letter, with an appointment time for their intervention telephone/video call. Control participants will be informed via telephone or email.

## Feasibility outcomes

The feasibility and acceptability outcomes are described in detail in Table 1 and include the recruitment and retention rates as well as app usage and engagement. These outcomes will be used to assess whether a future definitive trial could continue as per the current protocol, or if revisions are required before moving to the larger trial. The results of a power calculation will be considered alongside the recruitment and retention rates in order to estimate the number of participants that would need to be invited to provide the required sample size, to assess if this is feasible. In addition, if study enrolment is less than 30% or the 3-month retention rate is less than 65% we will consider if the trial procedures need modifying to make them more acceptable. Adaptations will be made to the assessment measures if the results indicate that these were not acceptable to participants or that participants were unable to complete them online. If more than 50% of the intervention participants do not download or use the app, or we are not able to deliver the behaviour change techniques (BCTs) to them as planned then this will trigger discussion about acceptability of the intervention. In lieu of clear published guidelines to base these values on these are pragmatic decisions that will trigger discussion about adaptation of the protocol. As part of the economic evaluation, a value of information analysis will be conducted. Value of information analysis helps ascertain the likely value of obtaining further information and therefore may provide useful information in the context of proceeding to a full RCT. While the listed criteria will be the primary criteria considered we will also examine the results from all data collected and any issue relating to successful trial delivery will inform decisions about progressing to a larger trial.

**Table 1 Tab1:** Feasibility and acceptability outcomes

Outcome	Measure
Recruitment rate	
Interest	Percentage of those potentially eligible (from medical records and clinician approval) who are interested and willing to answer further eligibility questions.
Enrolment	Percentage of participants who are interested and eligible who are randomised.
Acceptability of randomisation	The percentage of participants who withdraw upon being informed of allocation (within 1 week of randomisation). The percentage of potential participants who state that randomisation is their reason for declining to participate.
Feasibility of administering the intervention	The percentage of the intervention group who: - receive a behavioural support call. - self-report successfully downloading the app.
Acceptability of the intervention	Percentage of participants who report that no aspect of the intervention (leaflet, call, planner, app) was useful. Percentage of withdrawals from intervention group compared to control group. Percentage of reasons for withdrawal relating to the intervention.
Retention rate	The percentage of participants, in each group, who complete any of the T1 follow-up assessment measures.
Acceptability of outcome assessments	The percentage of participants who consent who complete any baseline assessments. Completion rates, in each group, for each of the assessments at: - baseline - follow-up
Willingness of participants to consent to linkage with HES/NCRAS registries for long-term follow-up	The percentage of participants who consent for this aspect of the study.
Acceptability of online assessments	The percentage of participants who require help from a researcher to complete questionnaires. The percentage of potential participants who give this method of data collection as a reason for declining to participate.
Acceptability of providing informed consent online	The percentage of potential participants that state that they are unable/unwilling to provide consent online.
Self-reported app usage and engagement	Percentage of participants in the intervention group who report using the app for less than a month.
The proportion of screened participants ineligible and reasons for ineligibility	The number of participants screened and deemed ineligible for each inclusion/exclusion criteria.
Potential sociodemographic biases in recruitment	Anonymised aggregate socio-demographics (age, gender, ethnicity, Index of Multiple Deprivation, cancer type, cancer stage, time since diagnosis, treatment completed and started) of potentially eligible participants (from medical records and clinician approval) who did not participate in the trial compared with the study sample characteristics.
Fidelity of intervention delivery in the telephone/video calls	Average percentage of required behaviour change techniques covered in 25% of participants’ intervention calls (randomly selected) scored against a checklist.
Contamination of the control group	The percentage of participants in the control group who report: • using Active 10 during the study period. • that a health professional recommended Active 10 to them during the study period.

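### The window for withdrawal on learning the allocation runs from randomisation, but intervention participants are told by letter and controls by telephone or email, so time observed after notification is shortened, probably more in the intervention arm

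*Protocol article*

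**What the plan says.** In the protocol article, Table 1 (section Feasibility outcomes) gives two measures for acceptability of randomisation. The one for people already randomised is "The percentage of participants who withdraw upon being informed of allocation (within 1 week of randomisation".

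The Randomisation section sets a different way of telling each arm. For the intervention arm: "Intervention participants will be informed about their allocation arm by letter, with an appointment time for their intervention telephone/video call". For controls: "Control participants will be informed via telephone or email". The article gives no dispatch time, notification date or rule to align the two arms.

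The row is worded as one percentage over all participants. Elsewhere Table 1 separates the arms explicitly, for example under acceptability of the intervention: "Percentage of withdrawals from intervention group compared to control group". That row has no one-week limit.

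On the use of the whole table, the article states: "These outcomes will be used to assess whether a future definitive trial could continue as per the current protocol".

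**The concern.** The outcome is meant to capture people who leave because of what they learn about their allocation. That reaction cannot begin before they learn it. A limit counted from randomisation spends part of the week on the time it takes to tell them. A posted letter ordinarily takes longer than a call or an email, so this loss is probably larger in the intervention arm.

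The error has one direction. Compared with a full week after notification, a week that starts earlier can only miss reactive withdrawals, so randomisation would look somewhat more acceptable than it is. If the figure is also tabulated by arm, equal reactions could appear as more withdrawal among controls. This is the only Table 1 measure aimed specifically at how randomised participants respond to their allocation.

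**Working it through.** **Inputs from the protocol article**

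- Window: 7 days from randomisation (Table 1).
- Channel: letter for intervention, telephone or email for control (Randomisation).
- Allocation: "participants will be individually randomised using minimisation with a 1:1 allocation ratio".
- Numbers: "A total of 90 participants will be recruited to account for potential loss to follow-up (assuming equal drop-out in both groups". If all 90 are randomised 1:1, that is 90/2 = 45 per arm.

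**Inputs the article does not give, taken as assumptions**

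- Delay *d* from randomisation to being informed: 0 days for controls, 1 to 5 days for the letter.
- True risk *p* of withdrawing in the 7 days after being informed, equal in both arms: 5% or 10%.
- The pattern of withdrawals over those 7 days.

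**The plan's own figure.** None is given for this outcome. The only sample-size figures are the target of 60 and the 90 to be recruited. 60/(1 − 1/3) = 90, but the one third is back-calculated as 1 − 60/90, so this shows consistency only. This point does not alter either number.

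**Step 1: time observed after notification = 7 − d.** For *d* = 1, 2, 3, 4, 5 this is 6, 5, 4, 3, 2 days, or 86%, 71%, 57%, 43%, 29% of a full week.

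**Step 2: withdrawals spread evenly over 7 days.** Share of intervention-arm events missed = d/7. Observed intervention rate = p × (7 − d)/7. People missed = 45 × p × d/7. Overall rate = average of the control rate *p* and the observed intervention rate.

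| Letter read on day | Share missed | Observed, p = 10% | Missed of 45 | Overall (true 10%) | Observed, p = 5% | Missed of 45 | Overall (true 5%) |
|---|---|---|---|---|---|---|---|
| 2 | 2/7 = 29% | 7.1% | 1.3 | 8.6% | 3.6% | 0.6 | 4.3% |
| 3 | 3/7 = 43% | 5.7% | 1.9 | 7.9% | 2.9% | 1.0 | 3.9% |
| 5 | 5/7 = 71% | 2.9% | 3.2 | 6.4% | 1.4% | 1.6 | 3.2% |

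Controls may also be told late. With a half-day delay at p = 10% they would show 10% × 6.5/7 = 9.3%.

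**Step 3: constant hazard instead of an even spread.** Observed rate = 1 − (1 − p)^((7 − d)/7). At p = 10% this gives 7.2%, 5.8% and 3.0% for days 2, 3 and 5, with overall rates of 8.6%, 7.9% and 6.5%. The result hardly changes.

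**Step 4: prompt reaction.** If everyone who withdraws does so within 2 days of being informed, the last withdrawals fall on day d + 2. For letters read on day 2, 3 or 5 that is day 4, 5 or 7. All lie inside the window, and nothing is missed.

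**After the fix.** Both arms have 7 days after notification. At p = 10% the expected count is 4.5 of 45 in each.

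**The case against.** The strongest reply is that the outcome is worded as withdrawal on being told, which suggests a quick reaction. Step 4 shows that a quick reaction to a letter that arrives in good time costs nothing. The article also places the first support call shortly after randomisation, and the letter carries that appointment, so a long postal delay is not what the investigators intend. This stands as a limit on size. It does not correct the definition, because no delay is stated and reactions need not be immediate.

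Second, nothing decisive hangs on this row. The numeric triggers in Feasibility outcomes concern enrolment below 30%, retention below 65%, and more than 50% of the intervention arm not downloading or using the app. Someone who leaves on day 8 still enters the comparison of withdrawals by arm. This stands too, although that comparison sits under acceptability of the intervention and does not isolate reaction to allocation.

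Two stronger readings are tempting, and the article does not support them. A reader might infer that withdrawals before notification are counted. They are not on the natural reading: being informed is part of the definition, and the parenthesis is an outer limit. A reader might also infer that the plan builds in a biased comparison between arms. The row specifies one overall percentage, so non-comparability arises only if someone splits it.

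**Conclusion.** The point holds as a modest flaw in definition. The window is tied to randomisation although the event is tied to notification, and the stated channels make the gap between the two probably longer in the intervention arm. The overall percentage can be too low. A split by arm, if made, would not be on equal follow-up.

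The size cannot be determined from the article. It runs from about zero, with prompt letters and prompt reactions, to about 29% to 71% of intervention-arm events missed, with an even spread over 7 days and a letter read on day 2 to 5. At an assumed 10% risk and 45 per arm, that upper scenario is about 1 to 3 people, and the overall figure would read 8.6% down to 6.4% in place of 10%. Delay, risk and pattern are all assumptions. The article does not support a claim that the progression decision or the sample size is affected.

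**What to change.** In Table 1, define the measure as withdrawal within 7 days of the date the participant is informed of the allocation, and report it overall and by arm. For controls, use the date of the call or email. For the intervention arm, use the posting date plus a fixed delivery allowance, or the date receipt is confirmed. List any withdrawals between randomisation and notification separately, so that the wording leaves no doubt about them.

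The cost is one extra date field and one reworded sentence, with no added participants or visits. The article states that recruitment had not started when it was submitted. Changing how either arm is notified is not needed, since a window that runs from notification gives both arms the same 7 days whatever the channel.

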## Measures

Measurement timepoints for the pilot are baseline (T0) and 3 months (T1; operationalised as 12–16 weeks from randomisation). When a participant provides consent they will be sent URL links to online questionnaires via email (with the option to complete these by phone with a researcher if they experience difficulties), and mailed weighing scales (Seca 803 if they weigh less than 150kg and Seca 813 if they weigh over 150kg), a tape measure (Seca 201), and an activPAL4micro accelerometer (PAL Technologies Ltd., Glasgow, UK).

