### Physical activity (T0 and T1)

Physical activity will be measured using thigh-worn activPAL4micro accelerometers that participants will be asked to wear continuously for seven days (PAL Technologies Ltd., Glasgow, UK). The activPAL protocol, which follows published recommendations for using the device and expert advice from the Trial Steering Committee, includes waterproofing the device using specially designed nitrile sleeves and waterproof dressings, asking participants to wear it continuously, and including the data for analysis if 3 days of data are available [61]. Participants will be mailed instructions on how to wear the device, a log-sheet to record when the device was worn and bedtimes and waketimes, and a freepost envelope to return it. The primary outcome of the future full RCT will be activPAL-assessed average daily brisk walking (> 100 steps/min). The activPAL has shown excellent reliability and validity in measuring step number and cadence (steps/minute) and has been used in other studies with people LWBC and clinical populations [62, 63]. Other physical activity outcomes that will be explored are total daily steps, minutes of light physical activity, standing time and sitting time.

Participants will also complete the Godin Leisure-Time Exercise Questionnaire (GLTEQ) [64], which has demonstrated favourable validity and reliability against objective measures of physical activity and is widely used in oncology research [64, 65]. The questionnaire will be adapted to add a question about duration of activities to allow calculation of minutes of MVPA, in addition to the leisure score index, a practice that is common in oncology research [65].

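### Retention is defined on completing any 3-month measure, so the 65% trigger and the number-to-invite estimate rest on an upper bound for activPAL completeness

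*Protocol article*

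**What the plan says.** The Retention rate row of Table 1 in the protocol article reads "The percentage of participants, in each group, who complete any of the T1 follow-up assessment measures".

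The Feasibility outcomes section uses retention twice. One use is a trigger: if "the 3-month retention rate is less than 65% we will consider if the trial procedures need modifying". The other is planning: "The results of a power calculation will be considered alongside the recruitment and retention rates in order to estimate the number of participants" who would have to be invited to reach the required size.

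The Physical activity section names activPAL-measured average daily brisk walking as the primary outcome of the future full trial. The device is worn for seven days and posted back, and the rule for use is "including the data for analysis if 3 days of data are available". The Measures section says that questionnaires are sent as online links, with help by telephone for those who have difficulty.

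Two further provisions bear on the point. Table 1 also lists completion of each assessment, by group, at baseline and at follow-up. The Feasibility outcomes section promises to adapt measures that prove unacceptable, to look at all the data collected, and to treat its cut-offs as pragmatic prompts for discussion.

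**The concern.** The pilot has to tell the team what fraction of randomised participants will supply the definitive trial's primary outcome. The retention rate as defined answers a different question: what fraction supply anything at all at 3 months. A participant who fills in one questionnaire but wears the device for two days, or does not return it, counts as retained.

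The questionnaires can be done online or by telephone. The device has to be fitted, worn for days and posted back. It is therefore reasonable to expect the two rates to differ, although the article gives no figure for the gap. If the any-measure rate is the attrition allowance for the definitive trial, that trial will recruit too few people with an analysable primary outcome. The 65% trigger could also stay silent while activPAL completeness is well below 65%.

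**Working it through.** **Inputs.** From the article: target 60 (30 per group) and 90 recruited (Sample size); trigger at 65% (Feasibility outcomes); retention on any 3-month measure (Table 1); a usable activPAL record needs 3 days (Physical activity). Not in the article, so assumed: c, the share of retained participants with a usable 3-month activPAL record, taken as 0.9, 0.8 and 0.7.

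**1. The plan's own figure.** The Sample size section says "A total of 90 participants will be recruited to account for potential loss to follow-up". With N = n/(1 − d), the implied loss is d = 1 − 60/90 = 33.3%, and 60/(1 − 0.333) = 90. No loss rate is stated, so this shows consistency only and is not an independent check.

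**2. Why the rate is an upper bound.** activPAL is itself one of the 3-month measures, so everyone with a usable record is retained by definition, but not the reverse. With R the any-measure rate, the activPAL rate is A = R × c with c ≤ 1, so A ≤ R.

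**3. At the trigger boundary.** 0.65 × 90 = 58.5, so the smallest count that does not fire the trigger is 59 (59/90 = 65.6%). With R = 0.65:

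| c | A = 0.65 × c | of 90 |
|---|---|---|
| 0.9 | 58.5% | about 53 |
| 0.8 | 52.0% | about 47 |
| 0.7 | 45.5% | about 41 |

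**4. When the two readings of the trigger disagree.** An activPAL-based 65% criterion fires while the any-measure one does not if R ≥ 0.65 and c < 0.65/R. That is c < 0.93 at R = 70%, c < 0.87 at 75%, c < 0.81 at 80% and c < 0.72 at 90%. The closer any-measure retention is to the cut, the smaller the device loss needed to matter.

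**5. Inflation of the definitive trial.** Per 100 analysable participants at R = 80% (assumed), inflating by R gives 100/0.80 = 125. Inflating by R × c gives 139 (c = 0.9), 157 (c = 0.8) and 179 (c = 0.7). Recruiting 125 would yield 90, 80 or 70 analysable instead of 100. The shortfall factor is c whatever the value of R.

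**6. Effect on power.** For a two-sided 5% comparison of two means, the power left is Φ((1.96 + z)√c − 1.96), where z is 1.2816 for planned 90% power and 0.8416 for planned 80%. It does not depend on the effect size or the SD.

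- Planned 90%: 3.2416 × √0.9 − 1.96 = 1.115, giving 87%; √0.8 gives 0.939 and 83%; √0.7 gives 0.752 and 77%.
- Planned 80%: about 76%, 71% and 65%.

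These figures assume that missing activPAL data are not recovered by the analysis.

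**The case against.** The strongest reply is that the plan already collects and reports what is needed. The row of Table 1 on acceptability of outcome assessments gives completion of every assessment at follow-up by group, and that includes activPAL. The Feasibility outcomes section says that unacceptable measures will be adapted and that any problem with trial delivery will inform progression. The 65% figure opens a discussion and authorises nothing. The planning sentence says only that the power calculation is considered alongside recruitment and retention; it does not make the any-measure rate the sole attrition factor. The power loss arises only if the team sets aside a completion rate that it will already hold. Every value of c above is assumed.

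Most of this stands, and it sets the severity. A reader might infer that missing activPAL data would go unseen; the documents do not support that. What remains is that neither numeric use names activPAL completion, no number is attached to it elsewhere, and the section calls its listed criteria the primary ones to be considered.

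Three further inferences are tempting and do not hold:

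- **That the trigger is pooled and hides unequal loss.** The text does not say that it is pooled. Table 1 defines retention by group and compares withdrawals between groups. This is at most an ambiguity.
- **That 65% contradicts the sizing, since 60/90 is 66.7%.** The sizing serves parameter estimation in the pilot, and the trigger prompts a review of procedures for the next trial. They need not coincide, and the smallest passing count of 59 is one participant short of 60.
- **That baseline completion by group loses those who consent but are never randomised.** The enrolment row and the row on consenters who complete any baseline assessment largely cover them.

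**Conclusion.** The point holds in a limited form, with moderate severity. As defined, the retention rate can only equal or exceed the proportion with a usable primary outcome, and the article attaches that rate to both of its numeric uses of retention. This follows from the text and needs no assumption.

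The size of the gap is not known from the document. If 70% to 90% of retained participants have valid activPAL data, the analysable number falls 10% to 30% short of what the any-measure rate suggests. At that shortfall a definitive trial planned at 90% power would have about 77% to 87%, provided the any-measure rate is used as the attrition allowance and nothing is recovered by the analysis. If nearly all retained participants return a usable record, the practical effect is negligible.

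**What to change.** In the Feasibility outcomes section and Table 1, define a primary-outcome completion rate: randomised participants with at least 3 days of valid 3-month activPAL data, divided by all randomised, reported by arm. Apply the existing 65% trigger to that rate, and name it as the attrition allowance in the sentence on estimating the number to invite. Keep the any-measure rate as a descriptive outcome.

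The cut itself need not move. A 67% cut, for example, would fire with exactly 60 of 90 complete (66.7%). Reporting by arm is enough. A rule decided by the worse arm would be noisy at 45 per arm, where the standard error near the cut is √(0.65 × 0.35/45), about 7 percentage points.

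The cost is a change of wording, since the data are already collected. The headline retention figure will be lower than, or at best equal to, the any-measure figure, and the trigger is more likely to prompt a discussion.
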